## Abstract

**Background:**

Postoperative surgical site infections cause substantial morbidity, prolonged hospitalization, costs and even mortality and remain one of the most frequent surgical complications. Approximately 14% to 30% of all patients undergoing elective open abdominal surgery are affected and methods to reduce surgical site infection rates warrant further investigation and evaluation in randomized controlled trials.

**Methods/design:**

To investigate whether the application of a circular plastic wound protector reduces the rate of surgical site infections in general and visceral surgical patients that undergo midline or transverse laparotomy by 50%. BaFO is a randomized, controlled, patient-blinded and observer-blinded multicenter clinical trial with two parallel surgical groups. The primary outcome measure will be the rate of surgical site infections within 45 days postoperative assessed according to the definition of the Center for Disease Control. Statistical analysis of the primary endpoint will be based on the intention-to-treat population. The global level of significance is set at 5% (2 sided) and sample size (n = 258 per group) is determined to assure a power of 80% with a planned interim analysis for the primary endpoint after the inclusion of 340 patients.

**Discussion:**

The BaFO trial will explore if the rate of surgical site infections can be reduced by a single, simple, inexpensive intervention in patients undergoing open elective abdominal surgery. Its pragmatic design guarantees high external validity and clinical relevance.

**Trial registration:**

http://www.clinicaltrials.gov NCT01181206. Date of registration: 11 August 2010; date of first patient randomized: 8 September 2010

## Background

### Rationale for the trial

Postoperative surgical site infections (SSIs) are one of the most frequent surgical complications and a major cause of postoperative morbidity, prolongation of hospital stay, healthcare costs and even mortality. An estimated 300,000 to 500,000 SSIs occur in the USA annually [1-4]. In Germany SSIs are the third most frequent cause of nosocomial infections and account for approximately 15% of the 400,000 to 600,000 nosocomial infections per year (60,000 to 90,000 cases) according to data from the Robert-Koch Institute (RKI) and the German Nationales Referenzzentrum für Surveillance von Nosokomialen Infektionen (NRZ) [5,6]. Data from the German Krankenhaus Infektions-Surveillance-System (KISS) estimate an even higher number of approximately 128,000 SSIs annually [6]. Furthermore, an estimated 7,500 to 15,000 patients die every year in Germany due to nosocomial infections [7,8].

Despite the implementation of preventive measures such as preoperative antibiotic prophylaxis [9-12] and antiseptic skin cleansing [9,13], SSI rates in prospective trials with adequate follow-up and standardized SSI definition in abdominal surgical patients remain high and vary from 14% to 32% [14-17]. Applying the SSI criteria of the Center for Disease Control (CDC) [9], which differentiate between superficial, deep and organ-space SSIs at postoperative day 30, Darouiche *et al*. reported an overall SSI rate of 16.1% in the control group (povidone-iodine skin preparation) of their randomized controlled trial (RCT) in patients with clean-contaminated abdominal surgery [18]. Seiler et al. reported similar numbers in a randomized multicenter trial comparing three different techniques of abdominal wall closure in abdominal surgical patients with SSI rates varying from 13% to 19% [19]. SSI rates following colorectal surgery seem to be even higher as was shown by Bennett-Guerrero and colleagues, who reported an overall SSI rate of 21% in the control group (and 30% in the intervention group) of their prospective multicenter RCT comparing the application of a gentamicin-collagen sponge versus no intervention in colorectal patients [20]. National data from the USA support these numbers [21].

Multiple studies have shown an increase in the mean length of hospital stay by 6 to 24 days if SSIs occur [4,22-25]. The resulting direct costs have to be added to the indirect costs such as loss of workforce or insurance payments resulting in substantial expenses for the healthcare system [26-28].

The most frequent pathogens causing postoperative SSIs in general and abdominal surgical patients are endogenous pathogens from the skin or gastrointestinal tract (KISS data 2005 to 2008, [29]). This implies that adequate protection of the surgical site by wound edge protectors might reduce the rate of postoperative SSIs.

### Previous trials

Several previous trials have investigated the effect of wound edge protectors on SSI rates in abdominal surgery and report mixed results. While some found beneficial effects [30-33] others reported no benefit [34-36]. Similarly, a randomized trial in 2011 in which wound protectors were introduced together with other measures as a bundle to reduce SSIs did not show a benefit [37]. The diverging results may be explained by trial design, since the mentioned trials were either performed in a single institution setting, had small sample sizes, lacked adequate blinding, standardization or used varying definitions of outcome variables (SSI definitions). Large multicenter randomized trials comparing the use of a wound edge protector with standard intervention (sterile towels) under standardized conditions and with defined outcome variable (CDC definition of SSIs) are lacking.

It is important to point out that BaFO will apply a circular plastic wound edge protector covering the whole width of the wound (skin, subcutaneous tissue, fascia and muscle; Figure 1) not other forms of surgical draping such as adhesive incise drapes for which beneficial [38,39] as well as non-beneficial results [40,41] have been reported. A Cochrane meta analysis of the latter intervention compared to no adhesive drapes found no evidence that iodine impregnated adhesive drapes reduce the SSI rate (relative risk 1.03, 95% confidence interval 0.064 to 1.66, *P* = 0.89) [42]. Interestingly, when the authors of the same meta analysis compared the use of non-impregnated adhesive drapes to no drape usage, they found the SSI rate significantly increased in the drape group (relative risk 1.23, 95% confidence interval 1.02 to 1.48, *P* = 0.03).

**Figure 1 F1:**
[figure not shown]
**Schematic drawing of the wound edge protectors used in the BaFO trial.** The protector consists of an impervious drape that covers the abdomen of the patient and is fixed to the skin with the help of adhesive tapes. It has a standardized size of 90 × 90 cm. The hole in the middle is connected to a flexible plastic ring that fits into the abdominal wound and protects the wound edges (skin, subcutaneous tissue, fascia and muscle) from contact with viscera, visceral contents and gloves, while allowing for visualization of the wound edges.

### Objective

BaFO aims to investigate whether the application of a circular plastic wound edge protector (Figure 1) reduces the rate of SSIs (within 45 days postoperatively) in abdominal surgical patients that undergo elective midline or transverse laparotomy by 50% (from 16% to 8%). As a secondary endpoint the difference in intraoperative core body temperature between the two study groups will be evaluated.

### Trial sites

The BaFO trial will be performed at 15 sites of the Trial Network (CHIR-*Net*) of the German Surgical Society (Deutsche Gesellschaft für Chirurgie (DGCH)). Most of these sites have participated in previous randomized controlled trials and all centers were adequately trained and prepared according to International Conference on Harmonisation of Technical Requirements for Registration of Pharmaceuticals for Human Use (ICH)-good clinical practice (GCP) rules for participation in this trial. CHIR-*Net* is funded by the German Ministry of Research and Education (Bundesministerium für Bildung und Forschung (BMBF); see funding information below).

## Methods/design

### Trial population and eligibility criteria

All general and abdominal surgical patients scheduled for elective open abdominal surgery requiring a median or transverse laparotomy will be eligible, given their ability to understand the extent and nature of the BaFO trial as well as their written informed consent. Patients participating in the BaFO trial must be 18 years of age or older, and the planned operation should be classified as clean or clean-contaminated as per the CDC definition [9]. Exclusion criteria are listed in Figure 1.

**Table 1 T1:** Exclusion criteria of the BaFO trial

**No.**	**Exclusion criteria**
1	ASA grade >3
2	Pregnant or lactating women
3	Midline or transverse laparotomy within the last 60 days prior to trial intervention
4	Planned relaparotomy within 30 days after trial intervention
5	Contaminated operations according to CDC definition [9]
6	Small abdominal operations without planned transverse or midline laparotomy (for example, appendectomy)
7	Concurrent abdominal wall infections
8	Severe immunosuppression, for example after: organ or bone marrow transplantation, concurrent steroid treatment with >10 mg prednisone daily (or an equivalent dose of any other steroid), concurrent infliximab treatment or treatment with an equivalent immunosuppressive substance, or chemotherapy within the last 2 weeks prior to trial intervention
9	Severe preoperative neutropenia (≤0.5 × 10^9^ cells/l)
10	Liver cirrhosis; Child-Pugh B or C [43]

ASA = American Society of Anesthesiologists; CDC = Centers for Disease Control and Prevention.

### Sample size

A total of 258 patients will be analyzed per group. Given an estimated drop out rate of approximately 15%, 600 patients will be randomized to 1 of the 2 treatment arms.

### Type of trial

Randomized, controlled, observer and patient blinded multicenter surgical trial with two parallel comparison groups.

### Recruitment and trial timeline

A total of 15 centers of general and abdominal surgery in Germany will participate in this trial. The centers vary from university hospitals to community hospitals and include certified centers for colorectal surgery (Darmzentren). All centers are members of the Trial Network (CHIR-*Net*) of the German Surgical Society. Physicians or nurses involved in the trial have been trained in ICH-GCP prior to initiation of the trial. Furthermore, all centers and participants were specifically instructed in study-specific procedures prior to the start of the trial. The centers will be supported by an ICH-GCP qualified flying study nurse from the CHIR-*Net* Surgical Regional Centre Munich to ensure protocol conforming data acquisition and trial interventions. Stratification according to center will be performed and all centers must recruit a minimum of 15 patients.

The duration of the recruitment phase is expected to be 30 months. The last follow-up will be performed a maximum of 45 days after the last patient underwent the trial intervention. Hence, the total duration of the trial is expected to be no longer than 32 months. The study flow is outlined in Figure 2.

**Figure 2 F2:**
[figure not shown]
**Flow chart of the BaFO trial.** F/U = follow-up; postop day = postoperative day; R = randomization; SSI = surgical site infection.

### Randomization and blinding

Randomization and blinding will be performed with the help of sealed, opaque, individually numbered envelopes, restricted to choosing one at a time. The envelopes contain data sheets with information regarding the group allocation and the randomization number. Both will be prefabricated by a biostatistician of the Technische Universität München (TUM; Munich, Germany). Randomization (visit 2, see Figure 2) will be performed after inclusion of the patient in the trial (informed consent, visit 1) or in the period between inclusion and the trial intervention (day of surgery) or at the day of surgery (visit 3). Randomization will be performed stratified by center. To assure balanced group sizes in the course of the accrual, a blockwise randomization is applied. Basic characteristics of the patient and day of randomization must be documented on the randomization sheets. Subsequently, randomization sheets must be dated, signed and stored away from the patient records, the trial documents and the investigator site file to ensure blinding. Patients, outcome assessors and the trial statistician will be blinded for the trial intervention. The outcome assessor (postoperative SSIs) will therefore neither be part of the surgical team that performs the trial intervention nor have access to the randomization sheets. Patients will be blinded since they are under general anesthesia during the operation and therefore will not be aware which intervention is used during the operation.

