#### Analysis

The primary analysis will be conducted according to the intention-to-treat (ITT) principle, that is, all included patients will be analyzed as randomized. Patients with missing primary outcome data will be considered as non-SSI cases if they belong to the control group and as SSI cases if they were randomized to the innovative treatment arm. For purpose of sensitivity analyses, per protocol and complete case analyses of the primary endpoint will be conducted and further appropriate and less conservative missing-value replacement strategies such as multiple conditional imputation [47] will be employed.

A planned interim analysis will be performed after recruitment and follow-up of 340 patients (two-thirds of the planned total). Due to this intended interim analysis, global α error adjustment is performed by the method of O’Brien and Fleming [48]. Therefore, evaluation of the primary efficacy endpoint will be conducted at a 0.005 level of significance (two sided) in the interim analysis and at a 0.048 level of significance (two sided) in the final statistical analysis.

Prespecified subgroup analyses or treatment group comparisons will be performed for: rate of superficial postoperative SSIs (according to CDC classification); rate of deep postoperative SSIs (according to CDC classification); rate of postoperative SSIs of organ space (according to CDC classification); rate of postoperative SSIs (total/superficial/deep/organ space) stratified by the National Nosocomial Infection Surveillance (NNIS) risk score [46]; rate of postoperative SSIs (total/superficial/deep/organ space) stratified by colorectal and non-colorectal operations.

Secondary analyses will be conducted in an explorative manner. Kaplan-Meier analysis and Cox regression analyses will be employed for analyses of time to event endpoints. The χ^2^ test will be used to compare frequency data between intervention groups. As appropriate, the Student t test, Mann–Whitney U test or analysis of covariance (ANCOVA) will be employed for group comparisons of quantitative data. The 95% confidence intervals will be provided for estimates of relevant effect sizes.

Safety analysis includes description and comparison of the frequency of adverse and serious adverse events in the two intervention groups.

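### Envelopes may be opened at any time from consent to surgery although the arm is needed only at draping: an avoidable source of randomized patients who never have the laparotomy

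*Protocol article*

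**What the plan says.** **Timing.** Under Randomization and blinding, the earliest option is directly after consent at visit 1. The same sentence then offers two later ones: "or in the period between inclusion and the trial intervention (day of surgery) or at the day of surgery (visit 3"). All three options are open to every site. The article does not ask for the laparotomy to be confirmed, or eligibility rechecked, before an envelope is opened. Table 2 marks the inclusion/exclusion check at visit 1 only.

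**Who learns the arm.** "The envelopes contain data sheets with information regarding the group allocation and the randomization number", so opening an envelope discloses the arm. "Patients, outcome assessors and the trial statistician will be blinded for the trial intervention"; the surgical team and whoever opens the envelope are not in that list.

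**Eligibility.** It rests on a plan: patients "scheduled for elective open abdominal surgery requiring a median or transverse laparotomy will be eligible". Table 1 likewise excludes by plan: "Small abdominal operations without planned transverse or midline laparotomy (for example, appendectomy").

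**Analysis.** Under Analysis, "all included patients will be analyzed as randomized". On missing outcomes the rule differs by arm: "Patients with missing primary outcome data will be considered as non-SSI cases if they belong to the control group", whereas a missing outcome in the protector arm is scored as an SSI.

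**The concern.** The two arms differ only in how the wound is covered during the operation, so nobody needs the allocation until draping. Opening the envelope days earlier gains nothing evident and has two costs.

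First, elective operations are sometimes cancelled, postponed or changed to a procedure without a midline or transverse laparotomy. A patient randomized before that happens remains in the primary analysis, possibly without having received either form of draping. If no SSI assessment follows, the missing-data rule may apply, and it works against the protector arm only.

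Second, staff who are not blinded may know the arm while cancellation, choice of procedure or withdrawal is still undecided. Sealed, numbered envelopes conceal allocation only until they are opened.

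**Working it through.** **Inputs from the article.** SSI rates 16% (control) and 8% (protector), 80% power, two-sided 5%, 258 per group, 600 randomized (Sample size calculation); final two-sided level 0.048 (Analysis). Equal allocation is assumed, giving 300 per arm.

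**Input not in the article.** *m* is the share of each arm randomized early and never undergoing the laparotomy. No value is given, so a range is shown.

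**Step 1: reproduce the plan's figure.** With the pooled-variance formula and no continuity correction,

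n = [1.960·√(2 × 0.12 × 0.88) + 0.8416·√(0.16 × 0.84 + 0.08 × 0.92)]² / 0.08² = (0.9007 + 0.3838)² / 0.0064 = 257.8, so 258 per group. This matches.

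**Step 2: reference power.** For rates p1 and p2 with mean p̄ and n per arm,

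power = Φ[(|p1 − p2| − z·√(2p̄(1 − p̄)/n)) / √((p1(1 − p1) + p2(1 − p2))/n)], with z = 1.977 for two-sided 0.048.

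At n = 300 and 16% v 8%: (0.08 − 1.977 × 0.02653) / 0.02633 = 1.046, so power is 85.2%. This assumes no dropout for any other reason.

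**Step 3: the same handling in both arms.** At m = 3%:
- counted as non-SSI in both arms: 0.16 × 0.97 = 15.52% v 0.08 × 0.97 = 7.76%, power 84.0%;
- excluded from both arms: 300 × 0.97 = 291 per arm at 16% v 8%, power 84.1%.

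The cost is about one percentage point. In numbers, 3% of 600 is 18 patients, within the 600 − 516 = 84 that the plan allows for dropout.

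**Step 4: coded as missing under the plan's rule.** Control rate = 0.16(1 − m); protector rate = 0.08(1 − m) + m.

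| Assumed m | Control | Protector | Difference | Power |
|---|---|---|---|---|
| 0% | 16.00% | 8.00% | 8.00 points | 85.2% |
| 1% | 15.84% | 8.92% | 6.92 points | 72.5% |
| 2% | 15.68% | 9.84% | 5.84 points | 56.6% |
| 3% | 15.52% | 10.76% | 4.76 points | 40.0% |
| 5% | 15.20% | 12.60% | 2.60 points | 14.5% |

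Each 1% removes 1.08 points from the expected difference, which reaches zero at m = 0.08/1.08 = 7.4%.

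**Step 5: attribute the loss.** At m = 3%, the same patients cost 85.2 − 84.0 = 1.2 points of power under non-SSI coding in both arms and 85.2 − 40.0 = 45.2 points under the plan's rule. About 44 of the 45 points therefore come from the missing-data rule.

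**The case against.** The strongest reply is that the large figures in step 4 belong to a different issue. Any 3% of missing outcomes, whatever the cause, would lower power in the same way, and the direct remedy for that lies in the missing-data rule. This stands. A reader might infer from the table that early randomization itself reduces power to 40%; steps 3 and 5 show that it does not.

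Nor does the article say that non-operated patients count as missing. Its CDC definitions (Table 3) require infection within 30 days of the operation, so non-SSI would be a natural coding for someone never operated on. This also stands, and is why both codings are shown.

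A reader might also suppose that every patient whose plan changes goes unexposed, including one whose operation turns out to be contaminated. The article does not support that. Such a patient can still have the laparotomy, receive the allocated draping and be assessed at the wound visits. A postponed patient may be operated on later, and one given another procedure may still attend follow-up.

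Finally, a reader might infer that the surgical team knows the arm before surgery and acts on it. The article does not say who opens the envelope. It requires the randomization sheets to be kept away from patient records, trial documents and the site file, and its Risks section calls the protector an established method that leaves the operation unaffected. Concealment at enrolment is intact because randomization follows consent. Arm-aware cancellation is possible, but it is not shown.

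What the reply does not remove is the window itself. It is an explicit choice in the text, not operational detail left to a fuller document; no other section closes it; and nothing in the article needs it.

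**Conclusion.** The point holds as a modest, inexpensive improvement to the design. The article allows allocation to be disclosed earlier than the intervention requires. It thereby admits avoidable randomized-but-not-operated patients to the intention-to-treat set and leaves room for decisions made with the arm known.

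The size depends on two things that the documents do not fix: how many such patients there are, and how their outcome is coded. Handled alike in both arms, an assumed 3% costs about one point of power. Coded as missing, 1% to 5% would bring power to between 73% and 15%, mainly through the asymmetric rule. All of these figures assume 300 per arm, alpha 0.048, equal shares in both arms and no other dropout. The calculation also attributes every such patient to early opening. Since day-of-surgery randomization is already allowed, the real share from this cause may be smaller. Sample size, endpoint and test are unaffected.

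**What to change.** In Randomization and blinding, delete the two earlier options and keep the day of surgery. State that the next envelope is opened as late as practicable before draping, after eligibility and the planned midline or transverse laparotomy have been reconfirmed, by someone other than the outcome assessor. Record the time as well as the date on the randomization sheet; the present text asks only for the day. Report patients randomized but not operated on, by arm.

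The cost is a short amendment and a site instruction. The drawback is that envelopes must be available in or near theatre. The article's Trial status section gives 323 patients recruited, so of the 600 planned the change could still cover 600 − 323 = 277, counted from that date.

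The change reduces how often the missing-data rule is triggered by non-operated patients. It does not repair the rule.

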### Interventions

Experimental intervention: all elective general or abdominal surgical patients undergoing a midline or transverse laparotomy for any cause will have their surgical incisions covered with a circular sterile plastic wound edge protector during the operation (see Figure 1).

Control intervention: draping of the surgical incision will be performed with standard sterile surgical dressings.

The schedule of trial interventions is presented in Figure 2.

**Table 2 T2:** Study visits of the BaFO trial

**Activity**	**Visit 1 (screening)**	**Visit 2 (randomization)**	**Visit 3 (operation)**	**Visit 4 (postop day 2)**	**Visit 5 (postop day 4)**	**Visit 6 (postop day 6)**	**Visit 7 (postop day 8)**	**Visit 8 (postop days 10 to 14)**	**Visit 9 (postop days 30 to 45)**
Demographics and baseline clinical data	X								
Inclusion/exclusion	X								
Physical examination	X								
Patient information and informed consent	X								
Blood sampling^a^	X								
Randomization		X							
Temperature measurement			X						
Wound documentation				X	X	X	X	X	X
Mibi swab^c^				X	X	X	X	X	X
Measurement of wound diameter				X					

^a^Blood sampling: Serum: sodium, potassium, creatinin, C-reactive protein, total protein, blood urea nitrogen, glutamic-pyruvic transaminase, glutamic-oxaloacetic transaminase, γ-glutamyl transpeptidase, pseudocholinesterase, alkaline phosphatase, glucose; blood count: leucocytes, erythrocytes, hemoglobin, hematocrit, mean corpuscular hemoglobin, mean corpuscular volume, mean corpuscular hemoglobin concentration, platelets; Coagulation: quick (international normalized ratio), prothrombin time.

^b^One blood sampling between postoperative day 4 to 8 (visits 5 to 7).

^c^In case of a surgical site infection, a microbiological swab according to local practice should be obtained for microbiological specification and antimicrobial testing.

